## Methods

### Study Design

This is a prospective, 2-arm, multicenter observational study of patients with primary headache disorders at medical institutions participating in the fifth phase of the national pilot project for collaborative treatment [28]. The study protocol was developed following the SPIRIT (Standard Protocol Items: Recommendations for Interventional Trials) guidelines (Multimedia Appendix 1) and registered with the Clinical Research Information Service of South Korea (registration KCT0010812; July 28, 2025) [32]. The study will be conducted as part of the Registry for Korean Medicine and Western Medicine Collaborative Treatment study, with participant recruitment scheduled from the date of institutional review board approval to December 12, 2025. The detailed study schedule, as outlined in the SPIRIT guidelines, is illustrated in Table 1. Additionally, a schematic diagram displaying the study flow and timing of assessments is presented in Figure 1.

**Table 1 table1:** Schedule of enrollment and assessments according to the SPIRIT (Standard Protocol Items: Recommendations for Interventional Trials) guidelines.

			Study stage						
			Enrollment		Baseline and allocation		Treatment and follow-up		
							6 weeks		12 weeks
**Enrollment**									
	Informed consent	✓							
	Inclusion and exclusion criteria	✓							
	Sociodemographic information and medical history			✓					
**Assessments**									
	MHDs^a^			✓		✓		✓	
	NRS^b^			✓		✓		✓	
	HIT-6^c^			✓		✓		✓	
	EQ-5D-5L			✓		✓		✓	
	EQ-VAS^d^			✓		✓		✓	
	Cost information					✓		✓	
	Hospital medical records and administrative data							✓	

^a^MHD: monthly headache day.

^b^NRS: numeric rating scale.

^c^HIT-6: Headache Impact Test.

^d^EQ-VAS: EuroQol visual analogue scale.

**Figure 1 figure1:**
[figure not shown]
Schematic figure displaying the study flow and timing of assessments. CEAC: cost-effectiveness acceptability curve; CT: collaborative treatment; EQ-VAS: EuroQol visual analogue scale; HIT-6: Headache Impact Test; ICER: incremental cost-effectiveness ratio; ITT: intention to treat; MHD: monthly headache day; NRS: numerical rating scale; PP: per protocol; QALY: quality-adjusted life year; UC: usual care.

### Participants and Treatments

The study participants comprise patients diagnosed with primary headache disorders who visit hospitals participating in the fifth phase of the collaborative treatment pilot project and receive either collaborative treatment or UC alone [28]. Patients receiving UC are those treated exclusively with either KM or WM, whereas collaborative treatment refers to treatment involving both KM and WM. To minimize treatment heterogeneity and ensure clinical rigor, the therapeutic procedures for both WM and KM are conducted in strict accordance with the standard clinical practice guidelines (CPGs) for headaches in South Korea [10,33,34]. Specifically, following these standard CPGs, WM interventions typically involve acute abortive medications (eg, nonsteroidal anti-inflammatory drugs and triptans) and prophylactic agents (eg, β-blockers, anticonvulsants, and antidepressants) tailored to the specific headache disorder. Similarly, KM interventions are standardized to include acupuncture, electroacupuncture, pharmacopuncture (herbal injection), chuna manual therapy, and herbal prescriptions as outlined in the corresponding CPGs. In the collaborative treatment group, these standardized modalities are integrated to maximize therapeutic synergy; for instance, a patient may receive WM pharmacotherapy for rapid pain relief concurrently with KM acupuncture or chuna therapy to relieve muscle tension and address functional imbalances. Conversely, the UC group receives monodisciplinary care consisting exclusively of either WM or KM modalities. To ensure consistency across multiple centers, all participating practitioners will undergo standardized training on the study protocol and clinical guidelines before study initiation. Furthermore, adherence to these treatment standards will be periodically monitored by the Monitoring Center for Korean Medicine and Western Medicine Collaboration (MCMC) throughout the study period.

A nonrandomized observational design was adopted to reflect real-world clinical settings where patient preference acts as a crucial determinant of treatment adherence and outcomes. Consequently, participants will exercise informed choice regarding their treatment modality. During the consultation, practitioners will provide comprehensive information on the expected benefits, potential side effects, and cost implications of both collaborative treatment and UC. On the basis of this shared decision-making process, patients will select their preferred treatment group, ensuring that the study findings mirror actual health care use patterns in South Korea. If a participant opts for collaborative treatment, one practitioner will initiate a collaborative treatment request to the other practitioner. Treatment choices can be adjusted at any time through consultation with practitioners, and all treatments will be recorded and monitored. Patients who agree to participate will be given detailed information about the study and all safety-related aspects before they provide informed consent. After obtaining written consent, a medical doctor or a KM doctor will assess the participant’s eligibility. Those who meet the inclusion criteria will be enrolled in the study and assigned an enrollment number to preserve anonymity. To ensure fair and open participation, announcements about the study will be made publicly available at the participating institutions.

### Inclusion Criteria

Inclusion criteria are as follows: (1) adults aged ≥19 years; (2) individuals with a primary diagnosis of primary headache disorders who are first-time outpatients at one of the participating institutions as systematically defined by the *International Classification of Diseases, 10th Revision* (*ICD-10*; G43 [migraine], G44.0 [cluster headaches and other trigeminal autonomic cephalgias], G44.2 [TTH], and G44.8 [other specified headache syndromes]); and (3) individuals who voluntarily agree to participate in the study or whose legal representatives provide both written and verbal informed consent.

### Exclusion Criteria

Exclusion criteria are as follows: (1) individuals covered by automobile insurance (ineligible for treatment under the collaborative treatment pilot project) [28], (2) individuals with difficulty understanding the research questionnaire, (3) individuals with difficulty adhering to the study schedule and follow-up assessments, (4) individuals deemed unsuitable for participation at the discretion of the investigator, and (5) individuals participating in the national pilot project for herbal medicine coverage under the NHIS [28].

### Sample Size Estimation

To determine the appropriate sample size, we referenced data from our preceding pilot study, which was a multicenter prospective observational study conducted across 5 medical institutions during the fourth phase of the national collaborative treatment pilot project (December 2023-December 2024). This pilot study aimed to assess the feasibility and preliminary clinical effectiveness of collaborative treatment versus UC in patients with migraine (*ICD-10* code G43) and other headache syndromes (*ICD-10* code G44; Clinical Research Information Service registration KCT0010198). On the basis of the analysis of 59 participants from this pilot study, the NRS values were derived (group 1: mean 1.85, SD 1.66; group 2: mean 2.48, SD 2.13). Using the G*Power program with a 2-sided significance level of .05 and power of 80% (α=.05) and adjusting for a 10% discontinuation rate, the total required sample size for the study was determined to be 312 participants.

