## Results

The study was funded in June 2025. This trial protocol was approved by the institutional review boards in July 2025. Participant recruitment commenced in August 2025, with a target enrollment of 312 patients across multiple clinical centers. As of December 2025, participant recruitment is ongoing. Baseline data collection includes sociodemographic characteristics, clinical history, and treatment preferences. Clinical outcomes (MHDs, NRS, and HIT-6), HRQOL (EQ-5D-5L and EQ-VAS), and economic measures (QALYs, ICER, and CEAC) are being systematically collected during the study period. Data collection is expected to be completed by December 2027, and results are expected to be published in summer 2028.

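### The sample size of 312 cannot be reproduced from the printed inputs, and the 80% power makes no allowance for arms that patients choose themselves

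*Protocol article*

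**What the plan says.** Sample Size Estimation gives the pilot NRS values as "group 1: mean 1.85, SD 1.66; group 2: mean 2.48, SD 2.13". Their source is described thus: "On the basis of the analysis of 59 participants from this pilot study". The calculation was run in G*Power at a two-sided .05 level with 80% power, and then "adjusting for a 10% discontinuation rate", after which "the total required sample size for the study was determined to be 312 participants". The section does not give the number before inflation, the SD or effect size entered, the pilot arm sizes or an allocation ratio.

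Participants and Treatments describes a nonrandomized design in which, after consultation, "patients will select their preferred treatment group". The same section allows the choice to be changed later.

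**The concern.** A reader who enters the printed means and SDs into the usual two-sample t test does not arrive at 312. The test needs more patients, so 312 enrolled with the planned 10% loss would give somewhat less than 80% power on those inputs.

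The arm sizes add a second difficulty. A single total with no allocation ratio implies equal arms, but here the split is an outcome of patient choice. For a fixed total, a marked imbalance lowers power, and the two pilot SDs differ enough that the direction of the imbalance matters. If the trial shows no clear NRS difference, readers will weigh that result against a power of 80% that the printed inputs do not support.

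**Working it through.** **Inputs from Sample Size Estimation.** Means 1.85 and 2.48; SDs 1.66 and 2.13; two-sided alpha .05; power 80%; loss 10%; total 312. My assumptions: a two-sample t test (the article names the program but not the test) and, in steps 1 to 3, equal arms.

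**Step 1. Attempt to reproduce 312.**
- Difference = 2.48 − 1.85 = 0.63.
- SD = √[(1.66² + 2.13²)/2] = √[(2.7556 + 4.5369)/2] = 1.910.
- d = 0.63/1.910 = 0.330.
- Normal approximation: n per arm = 2(1.960 + 0.842)²/d² = 144.2, so 145.
- Noncentral t: 145 per arm gives 79.95% power and 146 gives 80.2%, so 146 per arm, or 292 evaluable.
- Inflation: 292/0.9 = 324.4, so 325 (326 for equal arms). This is 13 to 14 more than 312.

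Multiplying by 1.1 instead gives 292 × 1.1 = 321.2, so 322. Using the simple mean of the two SDs (1.895) gives 143 per arm, 286 evaluable, and 286/0.9 = 317.8, so 318. None of these is 312.

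**Step 2. What would give 312?** Pool the SDs by degrees of freedom, with n₁ + n₂ = 59:

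SD = √{[(n₁ − 1)·1.66² + (n₂ − 1)·2.13²]/57}

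| Assumed pilot split (group 1/group 2) | SD | Evaluable | Enrolled, equal arms |
|---|---|---|---|
| 34/25 | 1.872 | 280 | 312 |
| 33/26 | 1.881 | 282 | 314 |
| 30/29 | 1.905 | 290 | 324 |
| 25/34 | 1.946 | 302 | 336 |

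A 34/25 split gives 280/0.9 = 311.1, hence 312 exactly. A 33/26 split also gives 312 if each arm is multiplied by 1.1 (141 × 1.1 = 155.1, so 156 per arm). So 312 corresponds to an SD of about 1.87 to 1.88, which is not printed and depends on a pilot split that is not printed.

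**Step 3. Power of 312 with equal arms, SD 1.910.**
- After 10% loss: 312 × 0.9 = 280.8, so 280 evaluable, 140 per arm.
- Standard error = 1.910 × √(2/140) = 0.228; 0.63/0.228 = 2.76; power from the noncentral t = 78.5%.
- With no loss at all (156 per arm): 82.8%.
- The loss that still leaves 292 evaluable is 1 − 292/312 = 6.4%.

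**Step 4. Power with unequal arms.** The stated SDs are kept separate: standard error = √(1.66²/n₁ + 2.13²/n₂), with Satterthwaite degrees of freedom and 280 evaluable in total. The splits are assumptions, because the article gives none.

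| Split | n₁ (SD 1.66) / n₂ (SD 2.13) | Standard error | Power |
|---|---|---|---|
| 1:1 | 140/140 | 0.228 | 78.5% |
| 60:40, lower-SD group larger | 168/112 | 0.239 | 75% |
| 60:40, higher-SD group larger | 112/168 | 0.227 | 79% |
| 2:1, lower-SD group larger | 187/93 | 0.252 | 70% |
| 2:1, higher-SD group larger | 93/187 | 0.232 | 77% |

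The groups are labelled only 1 and 2, so a reader cannot tell which direction corresponds to more patients choosing collaborative treatment.

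**The case against.** The best defence is that 312 may be entirely correct on the authors' own data. They know the pilot arm sizes. If these were 34 and 25 and the SDs were pooled accordingly, the calculation gives exactly 312. A condensed article need not print every intermediate figure. This stands: a reader might infer that the number is an arithmetic error, and the document does not support that. It does not make the number traceable, though, because the split is obtained only by solving backwards, and neighbouring splits give other totals.

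Second, the equal-arm shortfall is only 1.5 percentage points, well within the uncertainty of SDs from 59 patients. This also stands; on that ground alone no decision would change.

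Third, unequal arms are a possibility and not a fact, and they do not always cost power. A 60:40 split towards the higher-SD group gives 79%, no lower than equal arms. This stands too, and is why the unequal-arm figures must be shown as assumptions.

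A reader might go further and call 60% to 78% the realistic power. The lower end needs a 3:1 split with the lower-SD group larger, and nothing in the article predicts that. A reader might also quote about 69% for the covariate-adjusted model, by supposing that covariates explain 20% of group membership (140 × 0.8 = 112 effective per arm). That counts only the loss: if the same covariates explained 20% of the outcome variance, the effective number would return to 112/0.8 = 140 and power to 78.5%. Neither proportion is given, so no adjusted figure is supported.

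**Conclusion.** The concern holds in limited form. On the printed inputs, 80% power with 10% loss needs 325 to 326 enrolled, not 312, and 312 requires an unprinted SD of about 1.87 to 1.88. The equal-arm consequence is small: 78.5% against 80%. The larger weakness is that the power claim makes no allowance for self-selected arms. At the assumed splits examined, power is 75% or 79% (60:40) and 70% or 77% (2:1).

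These figures rest on a two-sample t test, a true difference of 0.63 points, the pilot SDs and the planned 10% loss. The calculation does not show a miscalculation or a trial that is badly underpowered.

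Study Design and Results also describe the end of recruitment in ways that need reconciling. That is a separate scheduling point and has no part in this conclusion.

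**What to change.** Keep 312. Then do one of two things in Sample Size Estimation:

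- replace the 80% claim with about 78% power for a 0.63-point NRS difference, with equal arms and 10% loss; or
- print the SD and the number before inflation that lead to 312, so that the 80% can be checked.

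In either case, add one sentence or a short table giving power at plausible unequal splits in both directions, and say which treatment each pilot group received so that the direction can be read.

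The cost is a few lines of text and, under the first option, a slightly less favourable power figure. No extra patients are needed and the planned analysis does not change.

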### Data Collection and Management

Data for the study will be collected through participant surveys using a standardized case report form (CRF). The CRF is designed to capture participants’ baseline characteristics, hospital medical records, and administrative data from each participating institution. This includes sociodemographic information, medical history, clinical indicators, and cost-related details. Administrative and medical data will be used to assess treatment costs associated with primary headache disorders, types and frequencies of treatment, medical expenses, duration of health care use, and types of services used. Trained and experienced researchers at each institution will be responsible for collecting both baseline and follow-up data. Face-to-face or telephone interviews will be conducted. All data will be entered and managed using the Internet-Based Clinical Research and Trial Management System developed by the Korea National Institute of Health. To protect participant confidentiality, all collected documents will use identification codes instead of personal names and will be stored as encrypted files, with access limited to authorized researchers. The MCMC will independently oversee data handling, storage, and validation throughout the study. This center, established under the Ministry of Health and Welfare as part of the fifth phase of the national pilot project, will serve as the study’s executive data management body. The monitoring center personnel will ensure compliance with the observational study protocol, authorize any modifications to the registry protocol, oversee the accuracy and appropriateness of data collection, and verify that informed consent has been properly obtained from all participants.

### Ethical Considerations

The study adheres to the principles outlined in the Declaration of Helsinki and follows good research practices as recommended by the Professional Society for Health Economics and Outcomes Research [35]. This study protocol was reviewed and approved by the institutional review boards of Wonkwang University Gwangju Oriental Medicine Hospital (approval WKIRB-2025-10) and Dongshin University Mokpo Oriental Medicine Hospital (approval DSMOH25-4). Written informed consent will be obtained from all participants or their legal representatives before enrollment. Participants will be fully informed about the study’s purpose, procedures, and potential risks and their right to withdraw at any time without penalty. To ensure privacy and confidentiality, all participant data will be deidentified and assigned a unique study identification code. Personal information will be stored separately from clinical data in encrypted files accessible only to authorized research personnel. No financial compensation is provided for participation.

### Measures

#### Baseline Characteristics

The participants’ baseline information will be collected on the first hospital visit. This includes age, gender, monthly household income (in KRW), history of treatment for primary headache disorders and other medical conditions, medication use, occupation and employment status, insurance status, and onset duration (duration from headache onset to first hospital visit).

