## Introduction

Headache disorders are among the most prevalent neurological conditions worldwide, affecting over 52% of the global population and contributing substantially to disability and health care costs [1,2]. According to the Global Burden of Disease 2019 study, headache disorders rank as the leading cause of years lived with disability worldwide [1,3]. In South Korea, National Health Insurance Service (NHIS) data from 2023 indicate that 580,292 patients were treated for migraine and 543,750 were treated for other headache disorders, such as tension-type headache (TTH), with total health care expenditures exceeding KRW 255.82 billion (US $172.6 million) [4]. Additionally, chronic headaches can lead to reduced productivity, depression, and insomnia [5,6].

Headache disorders are classified into primary and secondary types; primary headache disorders, encompassing migraine and TTH, are estimated to account for approximately 90% of all headache cases [7]. Primary headache disorders are typically managed with pharmacological interventions, whereas the priority for secondary headache disorders lies in identifying and treating the underlying cause [8]. Pharmacological treatments for primary headache disorders—such as nonsteroidal anti-inflammatory drugs and tricyclic antidepressants—often demonstrate limited long-term efficacy and may cause adverse effects [9-11]. Chronic headache in particular is frequently resistant to pharmacotherapy, and overuse of analgesics can exacerbate headache symptoms [9,12].

These substantial impacts underscore the urgent need for structured, multidisciplinary national strategies and alternative approaches for the management and treatment of primary headache disorders [5,13].

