### Statistical Analyses

Baseline data will be summarized using descriptive statistics such as percentages, frequencies, and means and SDs for both the UC and collaborative treatment groups. The UC group refers to participants receiving treatment exclusively with either KM or WM, whereas the collaborative treatment group includes those receiving both KM and WM. Data normality will be evaluated using the Shapiro-Wilk test and *Q*-*Q* plots. Between-group differences will be assessed using chi-square tests (Fisher exact test) for categorical data and the 2-tailed Student *t* test or ANOVA for continuous data. When normality or equal variance assumptions are violated, the Mann-Whitney *U* test and Kruskal-Wallis test will be performed.

Per-protocol and intention-to-treat (ITT) analyses will be conducted to assess clinical effectiveness and cost-effectiveness. To establish the ITT dataset, the proportion and mechanism of missing data will be evaluated using the Little test. If the data are identified as missing completely at random or missing at random, as defined by Rubin [55], multiple imputation will be performed [55,56]. Mean changes in clinical outcomes over time will be compared between groups as part of the effectiveness analysis. Furthermore, a generalized linear mixed model will be used to assess between-group effects at each time point. To rigorously control for heterogeneity and potential confounders, the model will adjust for fixed effects, including age, sex, headache history (onset duration), specific diagnosis, and comorbidities. While specific treatment modalities vary, reflecting real-world practice, the analysis adheres to the ITT principle to evaluate the effectiveness of the collaborative treatment strategy compared to UC rather than the efficacy of individual modalities. Subgroup analyses will be performed according to headache type (migraine, TTH, or other) and headache severity (episodic or chronic).

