## Discussion

### Anticipated Findings and Comparison to Prior Work

We hypothesize that collaborative treatment will provide greater reduction in headache frequency and intensity compared to UC while demonstrating its cost-effectiveness from a societal perspective. By incorporating real-world data from multiple medical institutions participating in the fifth phase of the national collaborative treatment pilot project, the study integrates multidimensional patient-centered measures to provide evidence supporting effective and sustainable collaborative treatment integration in headache treatment.

Previous studies on KM, WM, or collaborative treatment for headaches have shown potential benefits, including pain reduction and improved quality of life [10,18,19,22,57]. However, the evidence remains limited and inconsistent, often relying on single-center designs and short follow-up periods and lacking cost-effectiveness analyses, thereby reducing both generalizability and methodological rigor [17,18,58].

Unlike prior research, this study intends to address these gaps by using a multicenter prospective design with a comprehensive cost-effectiveness analysis, thereby aiming to provide more generalizable evidence on the clinical and economic value of integrating pharmacological and nonpharmacological interventions. Furthermore, this study follows the research framework previously applied in a study for facial palsy [24], supporting the feasibility of our approach.

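### Adjustment for chronicity is not assured: the only named headache-history covariate is a loosely defined onset duration, and neither episodic/chronic status nor baseline headache days is named in the model

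*Protocol article*

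**What the plan says.** All references are to the Protocol article.

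- **Allocation.** Under Participants and Treatments, "patients will select their preferred treatment group" after a consultation; nothing is randomized.
- **Covariates.** Under Statistical Analyses, the stated aim is "To rigorously control for heterogeneity and potential confounders", and "the model will adjust for fixed effects, including age, sex, headache history (onset duration), specific diagnosis, and comorbidities".
- **Definition.** Baseline Characteristics gives the history item as "onset duration (duration from headache onset to first hospital visit" and says nothing more about what counts as onset.
- **Chronicity.** The Introduction states: "Chronic headache in particular is frequently resistant to pharmacotherapy". Statistical Analyses then uses "headache severity (episodic or chronic" as a subgroup factor. It is not in the covariate list.
- **Related baseline data.** Table 1 and Clinical Effectiveness schedule MHDs at baseline, 6 and 12 weeks. Baseline Characteristics also lists headache treatment history and medication use. None of these is named as a covariate.
- **Second account of the model.** Strengths and Limitations says the mixed models handle baseline differences and injury mechanisms. The latter has no counterpart in the covariate list and does not fit primary headache.

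**The concern.** The eligible disorders (migraine, tension-type headache, cluster headache) recur. For a patient with years of migraine who attends during a two-day attack, the start of the disorder and the start of the attack both fit the wording of the item. An analysis plan can choose a transformation later, but it cannot separate two meanings once they share one field.

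The larger gap is chronicity itself. The protocol says chronic headache responds differently to drugs and treats the distinction as important enough for a subgroup analysis. Patients with long-standing or drug-resistant headache may plausibly prefer collaborative treatment. If so, chronicity is related to both group and outcome, and the named covariates reach it only indirectly, through onset duration, age, diagnosis and comorbidities. The report could then say that headache history was controlled when the main prognostic feature was not in the model. The direction of any bias cannot be told from the document.

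**Working it through.** The plan gives no figure on this point. The first step compares the texts; the rest is an illustration whose inputs are assumptions.

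**1. What each text supplies.**

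| Item | Collected at baseline | Named in model | Used elsewhere |
|---|---|---|---|
| Onset duration | yes, meaning of onset open | yes, sole history term | – |
| Episodic/chronic status | not listed as an item | no | subgroup factor |
| MHDs | yes | no | outcome |
| Treatment history, medication use | yes | no | – |

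Specific diagnosis does not replace chronicity. The subgroup plan lists headache type and episodic/chronic status as separate factors, so the protocol itself treats them as distinct.

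**2. How imbalance in chronicity becomes bias.** Assume a standardised chronicity score C, logit P(collaborative) = 0.8 C, and no true treatment effect. Numerical integration gives Cov(T, C) = 0.1752, where T is the group indicator and Var(T) = 0.25.
- Group difference in mean C = 0.1752 / 0.25 = 0.70.
- Squared correlation of T and C = 0.1752² / 0.25 = 0.123.

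Assume follow-up NRS = 0.5 C + error (SD 1.8). For scale, the pilot difference is 2.48 − 1.85 = 0.63.
- *Follow-up level:* 0.5 × 0.70 = 0.35.
- *Change from baseline, same slope of 0.5 at baseline:* (0.5 − 0.5) × 0.70 = 0.
- *Follow-up level adjusted for baseline NRS:* the within-group variance of C is 1 − 0.123 = 0.877. With an assumed error correlation of 0.5 between visits, the slope on baseline is (0.25 × 0.877 + 3.24 × 0.5) / (0.25 × 0.877 + 3.24) = 1.839 / 3.459 = 0.532. The bias is 0.35 × (1 − 0.532) = 0.16. Error correlations of 0.3 and 0.7 give 0.23 and 0.10.
- *Change, if chronicity alters the course (slope 0.25 at baseline, 0.5 at follow-up):* (0.5 − 0.25) × 0.70 = 0.18.

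A simulation of 1,000,000 patients at error correlation 0.5 gave 0.346, 0.001, 0.163 and 0.177 for the four cases.

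**3. How far a proxy helps.** If a covariate on its proper scale correlates r with C, the share of the bias left after adjustment is (1 − r²) / (1 − 0.123 r²). This holds for level or change.

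| r | 0.3 | 0.5 | 0.7 | 0.9 | 1 |
|---|---|---|---|---|---|
| Share left | 92% | 77% | 54% | 21% | 0% |

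The document gives no r for onset duration.

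**4. Coding.** Even where log-duration is the confounder itself (r = 1), entering raw days as a straight line leaves 0.166 / 0.348 = 48% of the bias at an assumed log-SD of 1, and 95% at a log-SD of 2. This is why a log or banded scale is suggested below.

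**The case against.** Much can be said for the plan.

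- Calling the item headache history points to duration of the disorder, not age of the attack. Enrolment is of "first-time outpatients at one of the participating institutions" and baseline data are taken at the first hospital visit, so the end of the interval is most naturally the enrolment visit. Read this way, the item is ordinary disease duration. This stands, and the end of the interval is not in dispute.
- Item wording may be settled in the CRF or its manual, which are not shown, and trained researchers collect the data. This also stands. Taken alone, the open meaning of onset would be missing detail.
- The covariate list is introduced as non-exhaustive, Strengths and Limitations mentions baseline differences, and baseline MHDs are available. So chronicity may yet enter the model. But the named list is what the article offers as rigorous control, and it omits chronicity.
- The plan compares mean changes, which removes any chronicity effect that is constant over time (step 2). This stands, and it rules out carrying the 0.35 over to the planned analysis. It does not remove an effect on treatment response, which is the kind the Introduction describes.

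A reader might infer that the covariate mixes attack age with disease age across sites and so cannot control confounding by chronicity. The documents do not support that. They report no rate of mixed recording, any residual-bias figure built on one would be invented, and duration may be a partial proxy. A reader might also infer that the item was carried over from a single-onset illness, because "this study follows the research framework previously applied in a study for facial palsy". That sentence, with the stray mention of injury mechanisms, is suggestive but says nothing about this item.

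**Conclusion.** The point holds in limited form. In a self-selected comparison, the one named history covariate has an open definition. The prognostic feature that the protocol itself singles out is left to a subgroup analysis, although baseline MHDs that would support adjustment are already collected. Adjustment for chronicity is therefore not assured; it is not shown to be impossible.

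The size cannot be fixed from the document. Under the assumed confounding, bias runs from about 0 (change from baseline, constant chronicity effect) through 0.10 to 0.23 (baseline NRS adjusted) to 0.35 (follow-up level alone), against a pilot difference of 0.63. If chronicity alters the course, change from baseline is biased too, by 0.18 in the example. All of this depends on the assumed strength of selection and of the chronicity effect. The case for changing the plan is that the remedy is nearly free, not that a large bias has been demonstrated.

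The label on the subgroup is a plain error: episodic versus chronic describes frequency or chronicity, not severity.

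**What to change.** 1. In Statistical Analyses, add episodic/chronic status at baseline, or baseline MHDs, to the named fixed effects. If status is derived from MHDs, state the cut-off and use one of the two, not both. For the MHD outcome itself, baseline should enter either as a response or as a covariate, not twice.
2. In Baseline Characteristics, define onset duration as time since the first headache of this type, up to the enrolment visit. State that it enters the model on a log or banded scale.
3. Relabel the subgroup as headache frequency or chronicity.
4. Reconcile the covariate list with Strengths and Limitations, and remove the reference to injury mechanisms.

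**Cost.** One or two model terms and one clarified CRF item. Baseline MHDs are already scheduled for every patient, so step 1 needs no new data if it uses them. For patients already enrolled (recruitment began in August 2025), time since first headache can be asked at the week 6 or 12 interview where that is still ahead. It does not depend on treatment, but it will carry some recall error.
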